## Abstract

**Background:**

In high-income countries (HICs), increased rates of survival among pediatric cancer patients are achieved through the use of protocol-driven treatment. Compared to HICs, differences in infrastructure, supportive care, and human resources, make compliance with protocol-driven treatment challenging in low- and middle-income countries (LMICs). For successful implementation of protocol-driven treatment, treatment protocols must be resource-adapted for the LMIC context, and additional supportive tools must be developed to promote protocol compliance. In Tanzania, an LMIC where resource-adapted treatment protocols are available, digital health applications could promote protocol compliance through incorporation of systematic decision support algorithms, reminders and alerts related to patient visits, and up-to-date data for care coordination. However, evidence on the use of digital health applications in improving compliance with protocol-driven treatment for pediatric cancer is limited. This study protocol describes the development and evaluation of a digital health application, called mNavigator, to facilitate compliance with protocol-driven treatment for pediatric cancer in Tanzania.

**Methods:**

mNavigator is a digital case management system that incorporates nationally-approved and resource-adapted treatment protocols for two pediatric cancers in Tanzania, Burkitt lymphoma and retinoblastoma. mNavigator is developed from an open-source digital health platform, called CommCare, and guided by the Consolidated Framework for Implementation Research. From July 2019–July 2020 at Bugando Medical Centre in Mwanza, Tanzania, all new pediatric cancer patients will be registered and managed using mNavigator as the new standard of care for patient intake and outcome assessment. Pediatric cancer patients with a clinical diagnosis of Burkitt lymphoma or retinoblastoma will be approached for participation in the study evaluating mNavigator. mNavigator users will document pre-treatment and treatment details for study participants using digital forms and checklists that facilitate compliance with protocol-driven treatment. Compliance with treatment protocols using mNavigator will be compared to historical compliance rates as the primary outcome. Throughout the implementation period, we will document factors that facilitate or inhibit mNavigator implementation.

**Discussion:**

Study findings will inform implementation and scale up of mNavigator in tertiary pediatric cancer facilities in Tanzania, with the goal of facilitating protocol-driven treatment.

**Trial registration:**

The study protocol was registered in ClinicalTrials.gov (NCT03677128) on September 19, 2018.

Contributions to the literature
Implementation of potentially sustainable, technology-based interventions is limited in low-and middle-income countries. mNavigator demonstrates how a digital case management system can be used to support implementation of resource-adapted treatment protocols in global oncology, with an eye toward sustainability.mNavigator relies on a strong theoretical framework, the Consolidated Framework for Implementation Research, to inform user-centered design, implementation, and evaluation.mNavigator is designed to be agnostic of health care system or country. While it is designed for use with clinical practice guidelines adapted for Tanzania, it could be adapted again and/or disseminated to other countries and contexts.

## Background

In high-income countries (HICs), protocol-driven treatment has led to substantial improvements in survival among pediatric cancer patients by reducing uncertainty in clinical decision-making, creating uniformity in the approach to diagnosis and treatment, and ensuring consistency across providers [1–4]. However, over 85% of the 400,000 children newly diagnosed with cancer each year live in low- and middle-income countries (LMICs) where differences in infrastructure, supportive care, and human resources limit implementation of protocol-driven treatment [4]. These challenges in LMICs necessitate protocol adaptation for available resources to achieve successful implementation of protocol-driven treatment. Yet, in many LMIC settings where resource-adapted protocols are available, suboptimal protocol compliance contributes to treatment abandonment, further exacerbating the 60% survival disparity gap between HICs and LMICs. The use of supportive tools can facilitate compliance with protocol-driven treatment by standardizing clinical decision-making, and incorporation of decision support, checklists, and improved data use. However, in LMICs, instances of, and evidence on the effectiveness of such supportive tools is lacking.

Digital health applications have been used as tools to support providers with implementation of standardized protocols for the integrated management of childhood illnesses in Tanzania, HIV care in South Africa, and antenatal care in Nigeria [5–11]. In the case of integrated management of childhood illnesses, provider compliance with the digital protocol increased by up to 30% compared to the use of a paper-based protocol [5]. In addition to the impact on protocol-driven treatment, digital health applications have been applied in low-resource settings to facilitate task shifting, improve work planning and coordination between providers, as well as enhance the performance of health workers [12–15]. These data support the use of digital health applications to improve compliance with protocol-driven treatment [16–18].

The goal of this early-stage effectiveness-implementation hybrid study is to develop a digital case management system, called mNavigator, to facilitate protocol-driven treatment for pediatric cancer, and evaluate its preliminary effectiveness in a tertiary care setting in Tanzania. Currently, resource-adapted treatment protocols for two pediatric cancers, Burkitt lymphoma and retinoblastoma, are approved for use at all pediatric cancer centers by the Tanzanian Ministry of Health, Community Development, Gender, Elderly and Children. However, compliance with these treatment protocols is low in pediatric cancer centers in Tanzania, making this an ideal LMIC setting for testing a digital health system for supporting protocol compliance. To our knowledge, mNavigator is the first digital case management system leveraging mobile devices and being developed for improving protocol compliance in pediatric cancer in LMICs.

## Methods/design

The elements of the mNavigator system are reported below consistent with the Template for Intervention Description and Replication (TIDieR) checklist (see Table 1), the SPIRIT checklist for protocols (Additional file 1 Table S1), and the World Health Organization trial registration dataset (Additional file 1 Table S2).

**Table 1 Tab1:** The TIDieR (Template for Intervention Description and Replication) Checklist*: Information to include when describing an intervention and the location of the information

Item number	Item	Where located **	
		Primary paper (page or appendix number)	Other ^†^ (details)
	BRIEF NAME		
1.	Provide the name or a phrase that describes the intervention.	____8________	______________
	WHY		
2.	Describe any rationale, theory, or goal of the elements essential to the intervention.	___13, Additional file 1 Table S4_______	_____________
	WHAT		
3.	Materials: Describe any physical or informational materials used in the intervention, including those provided to participants or used in intervention delivery or in training of intervention providers. Provide information on where the materials can be accessed (e.g. online appendix, URL).	___9-11_____	_____________
4.	Procedures: Describe each of the procedures, activities, and/or processes used in the intervention, including any enabling or support activities.	_13–18, table 2_	_____________
	WHO PROVIDED		
5.	For each category of intervention provider (e.g. psychologist, nursing assistant), describe their expertise, background and any specific training given.	__12_____	_____________
	HOW		
6.	Describe the modes of delivery (e.g. face-to-face or by some other mechanism, such as internet or telephone) of the intervention and whether it was provided individually or in a group.	__12-13________	_____________
	WHERE		
7.	Describe the type(s) of location(s) where the intervention occurred, including any necessary infrastructure or relevant features.	___9, Additional file 1 Table S3______	_____________
	WHEN and HOW MUCH		
8.	Describe the number of times the intervention was delivered and over what period of time including the number of sessions, their schedule, and their duration, intensity or dose.	____12_______	_____________
	TAILORING		
9.	If the intervention was planned to be personalised, titrated or adapted, then describe what, why, when, and how.	_14, figure 1___	_____________
	MODIFICATIONS		
10.^a^	If the intervention was modified during the course of the study, describe the changes (what, why, when, and how).	_____N/A_____	_____________
	HOW WELL		
11.	Planned: If intervention adherence or fidelity was assessed, describe how and by whom, and if any strategies were used to maintain or improve fidelity, describe them.	_assessed by data from app (protocol compliance), Tables 3&4_	_____________
12.^a^	Actual: If intervention adherence or fidelity was assessed, describe the extent to which the intervention was delivered as planned.	____N/A______	_____________

^a^ These items are not relevant to the protocol and cannot be described until the study is complete

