#### Intervention delivery

The users will use mNavigator during one-on-one interactions with patients and their caregivers. At the first interaction with each cancer patient, the users will register the patient. During subsequent interactions, users will:
Enter pre-diagnostic labs and imaging tests.Assign patients based on physician preliminary clinical evaluation to BL, Rb, or non-BL/Rb cohorts for further assessment.Complete and review pre-treatment staging and laboratory checklists for patients with preliminary Rb or BL diagnosis to facilitate protocol compliance.Deliver cancer educational information in video format.Review treatment guidelines with decision support algorithms to facilitate care coordination between mNavigator users and prescribing physicians.Enter information on changes in treatment plan, including referrals to outside hospitals, second line treatment, or palliation.Follow-up with patients to record health related outcomes (on treatment, off therapy, relapsed disease, etc.) and vital status.

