#### Informed consent

mNavigator will be used as the standard of care for patient intake and outcome tracking of pediatric cancer patients at BMC. All pediatric cancer patients at BMC will be registered and tracked in mNavigator. For research purposes, research staff (e.g., research coordinator, mNavigator users, etc.) will consent caregivers of any patients who receive a clinical diagnosis of Rb or BL for tracking their treatment information. Data for only those providing informed consent will be used in the research study (with the exception of historical data). For consenting patients, mNavigator will be used for treatment management with a typical treatment duration of 3 months for patient with BL and 4 months for patient with Rb.

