### Outcome measures

Study outcomes are summarized in Tables 3 and 4. Measurement of study outcomes is guided by the RE-AIM framework. In mNavigator, we will collect data points that will allow us to measure outcomes in the following domains:
Reach – e.g., proportion of eligible patients for whom protocol was used.Effectiveness – e.g., proportion of cases that abandoned care, with treatment completion and time from hospital presentation to confirmed diagnosisAdoption – e.g., proportion of providers who use the protocol, provider acceptability and satisfaction with mNavigator content, ease of delivery and credibilityImplementation/Compliance – e.g., proportion of protocol steps completed per patientMaintenance (measured in future studies)

**Table 3 Tab3:** Summary of outcomes related to intervention effectiveness and their measurement

Outcome	Measure	Data source
Change in protocol compliance (primary outcome)	Percent difference in protocol compliance with mNavigator and historical compliance. Protocol compliance is calculated as proportion of protocol steps completed, based on a compliance checklist.	mNavigator data from prospectively registered pediatric cancer patients from July 2019 – July 2020 and data extracted from paper charts for patients registered at BMC from 2015 – June 2019 entered into mNavigator
Change in treatment abandonment (secondary outcome)	Calculated as the difference in proportion of patients registered in mNavigator who abandoned treatment compared to historical controls who abandoned treatment. Treatment abandonment is defined as missing four or more consecutive weeks of treatment or follow-up while still on therapy.	Data from mNavigator (outcome form)
Change in treatment completion rate	Calculated as the proportion of patients registered in mNavigator who completed treatment compared to historical controls	Data from mNavigator (outcome form)
Change in time to diagnosis	Change in the number of days to diagnosis using mNavigator compared to historical controls. Time to diagnosis is computed as the duration from registration to diagnosis	Data from mNavigator (registration form; diagnosis form)

**Table 4 Tab4:** System-level outcomes related to the mNavigator application

Outcome	Measure	Data source
Usability^a^	System usability scale score ranging from 0 to 100. A SUS score above a 68 is considered above average and anything below 68 is below average.	10-point validated system usability scale

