Acceptability	Proportion of providers who would continue to use the app. Proportion of providers who would recommend the app to others.	Semi-structured interviews
Utilization	Number of forms submitted, stratified, by users, per month of implementation	Data from mNavigator (Mobile users statistics)
Reach	Number of patients registered in mNavigator during study period	Data from mNavigator (Mobile users statistics)
Stability	• Number of instances of mNavigator failure per month (all-causes) • Number of instances of CommCare failure per month (all-causes) • Number of instances of device • failure per month (all-causes)	Data from CommCare (Worker Activity and Daily Activity reports) cross checked with manual reports from Mobile users
Training	Number of hours of initial training as well as hours of ongoing support provided during the first month of Implementation	Manually recorded from Duke team members that are performing initial training
User-proficiency	Number of users who are proficient in use of mNavigator within first month of implementation	Data from CommCare (Worker Activity reports)
Time per form	Average time in minutes spent completing each form, stratified by form	Data from mNavigator (Mobile users statistics)
Time per patient	Total time in minutes spent entering patient data in mNavigator, from time of registration until an outcome is recorded. Calculated by summing time for completing each form by patient.	Data from mNavigator (Mobile users statistics)

^a^System Usability Scale developed by John Brooke is available from www.usability.gov

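### Fidelity is given as the primary outcome, and tabulated Reach is a count fixed by universal registration, so no tabulated measure shows whether the decision support was used for Burkitt lymphoma and retinoblastoma patients

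*Protocol article*

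**What the plan says.** **Fidelity.** In Table 1 (Methods/design), item 11 asks how fidelity is planned to be assessed. The entry is "assessed by data from app (protocol compliance), Tables 3&4".

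**Primary outcome.** Table 3 compares compliance under mNavigator with historical compliance. It defines the score thus: "Protocol compliance is calculated as proportion of protocol steps completed, based on a compliance checklist". The Outcome measures text uses the same quantity, per patient, as its example for the RE-AIM Implementation domain.

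**Reach.** The Outcome measures text gives as its example the "proportion of eligible patients for whom protocol was used". Table 4 gives "Number of patients registered in mNavigator during study period". The Phase 2 Informed consent section states: "All pediatric cancer patients at BMC will be registered and tracked in mNavigator".

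**Other usage measures in Table 4.** Utilization is "Number of forms submitted, stratified, by users, per month of implementation". Time per form is "Average time in minutes spent completing each form, stratified by form". There are also time per patient and a count of proficient users from activity reports.

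**How the support is meant to work.** Under Intervention delivery, users are to "Review treatment guidelines with decision support algorithms to facilitate care coordination between mNavigator users and prescribing physicians". The same section places use of the app within one-on-one contacts with patients and caregivers.

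**Fidelity data outside the tables.** Quantitative data collection plans periodic observations, or surveys and/or checklists, on several areas. One is fidelity and quality of implementation, including how the app was used in practice. User interviews and thematic analysis of observation notes are also planned.

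**The concern.** This is an effectiveness-implementation hybrid study whose results are meant to inform roll-out to other centres. Such a study needs a measure of delivery that stands apart from the effect. If compliance does not rise, readers will ask whether the tool went unused or was used without benefit. If it does rise, they will ask whether the rise goes with use of the tool.

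When fidelity is read from the compliance score, a low score counts as poor fidelity and a high score as good fidelity, so neither question is answered. Tabulated Reach does not help, because a policy of registering everyone determines it. The form count shows activity, but not whether guidance was in front of the team when a decision was made.

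**Working it through.** This is mainly a comparison of definitions. The arithmetic concerns Reach only.

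**Step 1: fidelity against the primary outcome.** Item 11 names protocol compliance. Table 3 defines protocol compliance as the share of checklist steps completed and makes the change in it primary. The RE-AIM Implementation example is that same share. One score therefore serves as fidelity, as implementation, and as the quantity whose between-period difference is the effect.

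**Step 2: what tabulated Reach will show.** Inputs from Sample size and recruitment are about 150 new pediatric cancer patients a year, of whom about 50 have BL or Rb. The Study setting section gives 35%, and 0.35 × 150 = 52.5, which agrees.

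- Non-BL/Rb children: 150 − 50 = 100.
- Share of the Reach count: 100 / 150 = 67%.

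Under Intervention components, the forms for these 100 children neither track treatment nor incorporate guidelines. The table below varies the number of BL/Rb patients whose treatment module was used. These numbers are assumed, to show the range.

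| BL/Rb patients with module used (assumed) | Table 4 Reach | Proportion of eligible patients |
|---|---|---|
| 0 of 50 | 150 | 0% |
| 25 of 50 | 150 | 50% |
| 50 of 50 | 150 | 100% |

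The tabulated figure does not move across the whole range. The figure described in the text does.

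There is a further ambiguity. About 200 historical BL/Rb records are to be abstracted into the same app, and Table 4 does not say that they are excluded. If they were counted, Reach would read 150 + 200 = 350.

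**Step 3: the remaining Table 4 measures.**

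- Utilization counts forms by user and month. A form entered before a treatment cycle and one entered after it count the same.
- Time per form and time per patient are durations in minutes. They do not place the entry before or after the care decision.
- User proficiency describes users in the first month, not patients.

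The article's own procedures show that a completed form need not mean support at the point of care: historical charts are entered in the app after care has ended.

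**Step 4: the data outside the tables.** The observations, surveys or checklists are periodic and alternative to one another. The article does not tie them to whether support came before the decision. Part of what they describe is whether protocol steps were followed, which overlaps with the outcome. The audit covers the first 5 enrolled BL/Rb patients and then 1 in 10. With 50 patients, that is 5 + 45/10 = 9.5, or about 9 to 10 records. The follow-up action stated for it is correcting programming errors, not judging the timing of use.

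**The case against.** The strongest reply is that the article does plan separate fidelity data. Quantitative data collection lists fidelity and quality of implementation as an area of its own and names use of the app and following of protocol steps as two things. Interviews and observation notes add to this. That stands. A reader might infer from Tables 1, 3 and 4 that the trial cannot tell prior use of decision support from later filling-in. The documents do not support that reading, because these data may reveal it.

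Other parts of the reply also have weight:

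- **Item 11 is partly a pointer.** Its column asks where information is located, and it sends the reader to both tables. Even so, compliance is the only measure it names, and it omits the separate fidelity data.
- **Exposure and effect are not literally one number.** Exposure is the period (historical or mNavigator), and the effect is the difference between periods. The overlap lies in using the prospective compliance score as the fidelity measure too.
- **The RE-AIM text gives examples, while Table 4 lists system-level outcomes.** This softens the conflict over Reach but does not remove it: the same term is a proportion based on use in one place and a bare count in the other.
- **Late entry is not shown to occur.** The plan is to use the app during patient contacts. Offline operation permits entry at the point of care and is no evidence of delay. One of the four users is a junior physician and another has clinical officer training.
- **A condensed article may leave detailed fidelity definitions to the full protocol.** That excuses missing detail. It does not excuse the stated choice of the primary outcome as fidelity, or two definitions of Reach.

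**Conclusion.** The point holds in this form: Tables 3 and 4 define no quantitative fidelity measure independent of the primary outcome, and tabulated Reach conflicts with the text and carries no information on use. Reach will be about 150 whether the BL/Rb modules are used for none or all of about 50 patients, and about 67% of it consists of children whose forms contain no guidelines. This rests on the article's anticipated volumes and on registration being complete.

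The planned observations and interviews limit the damage but are not tied to the order of support and decision. It would go too far to say that the trial has no means of detecting after-the-fact entry, or that such entry is happening. The primary comparison itself is not altered by this point. What is weakened is the interpretation of its result and the implementation findings meant to guide scale-up. The change is worth making.

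**What to change.** 1. **Reach (Table 4).** Replace the count with the number of BL/Rb patients whose BL/Rb treatment-module forms were used, divided by all BL/Rb patients registered prospectively. Exclude abstracted historical records. Include non-consenters only as an aggregate count in the denominator, since the consent section restricts research use of their data. This matches the Outcome measures text. The count of all registrations can stay under another name.

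2. **TIDieR item 11 (Table 1).** Cite the fidelity data planned under Quantitative data collection, together with a usage measure, in place of protocol compliance.

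3. **Timeliness, if the platform stores form-entry dates.** This is an assumption, because the article mentions only durations. Report descriptively the share of decision-support and cycle-planning forms entered on or before the recorded treatment date. Restrict it to forms meant to precede a decision, because result-entry forms necessarily follow the test. Count expected forms that were never opened as not delivered, so that the measure is not limited to steps that were carried out. Dates alone cannot order events within a day, and the report should say so.

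**Cost.** Items 1 and 2 need wording changes in Tables 1 and 4 and data already in the app. Item 3 needs a short extract if the dates exist. Reported Reach will be less favourable, and any comparison of compliance by timely use is descriptive only. The primary outcome, the sample and patient care are unchanged.
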